**Table 1 Tab1:** **Information obtained from DoD chart abstraction: baseline polytrauma injury characteristics**

Type of variable	Information
Demographics	Age, sex, race/ethnicity and service branch
Initial Injury Information	Date, primary cause/mechanism
Vascular Extremity Details	Arterial/venous injury location, pre/post repair details, and complications.
Ortho/Nerve Extremity Details	Associated soft tissue/bone/nerve injuries, methods of repair, flap status.
Follow Up Care	Dates, location, and CT/MRI/Angio/Duplex studies.
Functional/ Amputation status	Limitations, context of amputation if relevant

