To address the second aim, characterize the preventive services received by individuals with vascular repair and related outcomes, we will first compute the proportion of patients who receive antiplatelet agents, statins, annual duplex ultrasound, and vascular specialty care (and categories described above), and the percent patency each year for individuals without amputation. We will then examine the relationship between percent patency and preventive care using random effects analyses that models the vascular repair patency as a linear function of the indicator of receiving antiplatelet agents, statins, duplex ultrasound [51, 52], and other covariates/confounders (e.g., number of limbs affected, any initial, early or late amputations, mental health comorbidity, TBI diagnosis, and pre-existing chronic disease states such as atherosclerosis, diabetes, peptic ulcer disease), where the random effect is used to adjust for the within facility correlation, and the inverse of the propensity score for receiving antiplatelet agents/statins/yearly duplex ultrasound is adjusted for as weights. The adjustment of the propensity score for receiving antiplatelet agents/statins/yearly duplex ultrasound will minimize the estimation biases due to confounding by indication. We will also create different cut points (e.g. 75%, 50% patent), and use a binary outcome model. If Vascular Preventive Care processes are associated with positive patient outcomes, there will be support for these care processes as best practices.

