We will also conduct generalizability analysis using the inverse propensity probability weight technique. [53, 54] The goal is to examine whether the outcome model derived from the VA IILS patients (as described above) can be generalized to the non-VA IILS patients. We first derive model estimates for the VA cohort, then compute the propensity score for receiving non-VA care by modeling the log-odds of receiving non-VA care (vs. VA care) as a linear function of baseline covariates. The inverse propensity weighting is used to calibrate the outcome model derived from the VA IILS patients to the non-VA IILS patients. Finally we assess model generalizability by comparing model estimates between the VA vs. non-VA patients using the diagnostic method by Stuart et al. [55] This generalizability method does not require collecting outcomes for non-VA patients. However the credibility of this method relies on the “ignorability” assumption to hold true: conditioning on the covariates, the counterfactual outcomes of the non-VA patients (the patency outcomes should they receive VA care) would have been the same as the outcomes of the VA patients, and similarly, the counterfactual outcomes of the VA patients (the patency outcomes should they receive non-VA care) would have been the same as the outcomes of the non-VA patients.

Based on preliminary data from the TRACC study, we anticipate that the proportion of OEF/OIF/OND VA patients with ILLS will receive antiplatelet agents/statins/or yearly duplex ultrasound will be no greater than 44.7%. We also assume that the mean vascular repair patency falls between 50%-60%, and that the increased patency due to receiving antiplatelet agents/statins/or yearly duplex ultrasound is no less than 12% (conservatively). Under these conditions, the study will have ≥0.84 power to determine if Vascular Preventive Care processes are associated with positive patient outcomes.

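### The Aim 2 model relates patency status to VA preventive care without restricting to, or adjusting for, repairs still open when VA care begins, so earlier closures bias the association in a direction that cannot be known in advance

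*Protocol article*

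**What the plan says.** All references are to the protocol article, the only document at hand.

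- **Outcome.** The second aim in the Analytic plan first computes the proportions receiving each kind of care "and the percent patency each year for individuals without amputation". It then fits a random-effects analysis that "models the vascular repair patency as a linear function of the indicator of receiving antiplatelet agents, statins, duplex ultrasound", plus covariates. A binary version follows: "We will also create different cut points (e.g. 75%, 50% patent), and use a binary outcome model". Each of these is a level or status of patency. None is a loss of patency. Under the first aim, by contrast, the same section names limb salvage survival time and time to amputation.
- **Adjustment.** The random effect is for facility: "where the random effect is used to adjust for the within facility correlation". The covariates, given as examples, include "number of limbs affected, any initial, early or late amputations, mental health comorbidity, TBI diagnosis" and pre-existing chronic disease. Patency at VA entry, time since repair and earlier patency are not named. Inverse propensity weights for receiving care are used, but their covariates are not listed.
- **Entry and timing.** Study sample requires a vascular repair done in theatre. It does not require that the repair be open on reaching the VA. The Aims section describes the preventive care as provided by the VA, and VA medical chart abstraction starts at VA entry.
- **Power.** The assumption is that "the increased patency due to receiving antiplatelet agents/statins/or yearly duplex ultrasound is no less than 12% (conservatively"), with mean patency of 50% to 60%, at most 44.7% receiving care, and power of at least 0.84.
- **Data on earlier status.** Table 1 lists, under DoD follow-up care, "Dates, location, and CT/MRI/Angio/Duplex studies". Table 3 lists VA imaging of the repair and additional procedures on the limb.

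**The concern.** Preventive care can act only on a repair that is still open. A repair that closed during the DoD phase enters the Aim 2 model as a failure whatever the VA then does, unless it is re-opened. Two things follow.

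First, closed repairs carry no information about the effect of care, and they pull the contrast towards zero if they are spread evenly over treated and untreated.

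Second, they may well not be spread evenly. A known closure can lead to less surveillance and treatment, or a failing repair can attract more. Earlier closure then determines both the exposure and the outcome, which is confounding by a variable the article does not name.

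The stake is the use made of the result: the article says that a positive association will support these care processes as best practices.

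**Working it through.** **Inputs.** From the article: N about 700 (Study sample; the power paragraph gives no N), 44.7% receiving care, mean patency m = 50% to 60%, and a gain of 12, read as percentage points. Assumed, because not stated: two-sided alpha 0.05, no clustering, and f, the fraction of repairs closed at VA entry.

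**1. The plan's own figure.** Groups: n1 = 0.447 × 700 = 312.9 treated, n0 = 387.1 untreated. With difference d, p0 = m − 0.447d and p1 = p0 + d. Power = Φ[(d − 1.96·SE0)/SE1], where SE0 uses the pooled proportion and SE1 the separate ones.

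For m = 0.55 and d = 0.12: p0 = 0.496, p1 = 0.616, SE0 = 0.0378, SE1 = 0.0374. Power = Φ[(0.12 − 0.0741)/0.0374] = Φ(1.225) = 0.890. Over m = 0.50 to 0.60 it is 0.886 to 0.900. This satisfies the stated 0.84 or more, though it does not reproduce 0.84 itself.

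**2. Closure unrelated to care.** If d is the effect among repairs open at entry, the difference over all repairs is d(1 − f). The last two columns give the power of the status model on all 700, and of the same model restricted to open repairs (N = 700(1 − f), mean patency m/(1 − f), 12 points, 44.7% treated).

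| f | Difference over all repairs | Power, all repairs | Power, open repairs only |
|---|---|---|---|
| 10% | 10.8 | 0.81–0.83 | 0.86–0.89 (N = 630) |
| 20% | 9.6 | 0.72–0.73 | 0.83–0.91 (N = 560) |
| 30% | 8.4 | 0.60–0.62 | 0.84–0.97 (N = 490) |

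Conversely, for the 12 points to hold over all repairs, the effect among open repairs must be 12/(1 − f) = 13.3, 15.0 or 17.1 points. The range stops at 30%: with 40% closed and 60% patent overall, every open repair would have to be patent (0.60/0.60) and no 12-point difference could exist.

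**3. Closure related to care, with no true effect.** Take f = 20%, overall patency 55%, and care reaching 25% of closed repairs but 44.7% overall.

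- Patency among repairs open at entry: 0.55/0.80 = 0.6875, the same with or without care.
- Open and treated: 0.447 − 0.20 × 0.25 = 0.397 of all repairs. Open and untreated: 0.80 − 0.397 = 0.403.
- Observed patency, treated: 0.397 × 0.6875/0.447 = 61.1%.
- Observed patency, untreated: 0.403 × 0.6875/0.553 = 50.1%.
- Spurious gain: 11.0 points, almost the whole assumed effect.

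The spurious difference is zero when closed repairs receive care at the overall 44.7% and turns negative above that share.

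**4. If the model is yearly.** A simulation over five years assumed permanent closure at 15% a year without care and 7.5% with it, a true risk ratio of 0.50. With care fixed over time, the ratio of non-patent prevalence was 0.55, 0.73 and 0.79 for f = 0, 20% and 30%. With care varying by year it was 0.82, 0.90 and 0.92. The ratio of new closures among open repairs stayed at 0.50.

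**The case against.** A reader might infer three stronger points that the article does not support.

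- **That the effect is necessarily diluted.** Dilution requires earlier closure to be unrelated to care. Step 3 gives the opposite direction.
- **That the power statement is wrong.** The 12 points stand beside the 50% to 60% mean patency, so they read as a gain in overall patency. On that reading the stated power is met at N = 700 and 44.7% treated. The losses in step 2 apply only if the 12 points came from repairs open at entry, which nothing in the article says.
- **That one old failure is counted again every year.** The yearly wording belongs to the descriptive step. The model sentence gives no time unit, and the 75% and 50% cut points suggest a graded measure. Step 4 therefore holds only on a yearly reading. Closures before VA entry matter on either reading.

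Other objections have weight. The covariates are introduced as examples, Previously collected data reserves DoD variables for control or stratification, and an article may leave detail to the full protocol. But the article does fix the outcome, model, random effect and weighting, and its named covariates omit the one that decides whether care could have worked.

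Table 1 shows that imaging studies were recorded, not that a patency result exists close to VA entry. The Background says most military facilities lack a vascular surgeon or vascular laboratory for long-term surveillance, so many repairs may be unclassifiable.

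Closure can also be reversed by a later procedure. For that reason, and because duplex is both an exposure and a means of detecting loss, replacing status altogether by first loss of patency is not clearly better.

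**Conclusion.** The concern holds in this form: the Aim 2 model, as described, mixes repairs that VA care could still protect with repairs already closed when that care began, and neither the facility random effect nor the named covariates separates them. The bias is towards the null if earlier closure is unrelated to care. It runs away from the null if closed repairs receive less care, and it masks or reverses a benefit if they receive more.

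Propensity weights do not cure this unless entry patency is in them. Even then the averaged difference would still be scaled by 1 − f, so restriction is needed as well as adjustment.

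The article gives neither the closed fraction nor its relation to care. The 8.4 to 10.8 points and the spurious 11.0 points are therefore illustrations of plausible size, not estimates. The stated power stands unless the 12 points were derived from repairs open at entry; the source of that figure should be stated.

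**What to change.** 1. Classify each repair at VA entry as open, closed or unknown, from the last DoD follow-up study (Table 1) or the first VA study.
2. Fit the Aim 2 model among repairs not known to be closed at VA entry. If the model is yearly, say so, and require that the repair is not known to be closed at the start of that year, with re-entry after a documented re-opening.
3. Measure care before the patency assessment it is related to.
4. Include entry status (open or unknown) in both the outcome model and the propensity model.
5. Add a sensitivity analysis limited to repairs documented open at entry, since some of the unknown group will in fact be closed.
6. Report the numbers closed and unknown at entry, and keep overall percent patency as a descriptive result.
7. State whether the 12 points refer to all repairs or to those open at entry.

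The cost is analysis wording and the coding of entry status from imaging already to be abstracted. The downsides are fewer repairs in the model and possibly a large unknown group. Loss will also be detected more often in scanned patients, so the duplex association needs a cautious reading under any version of the outcome.

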### Studies examining long term outcomes associated with vascular interventions are limited

In the Global War on Terror Vascular Initiative (GWOT VI) Rasmussen and colleagues defined the patterns and types of injuries [5, 14] as well as short term outcomes of using temporary vascular shunts [6], efficacy of incorporating endovascular procedures [4], and selective repair of tibial artery injuries [15]. OEF/OIF/OND vascular trauma occurred at a 5-times higher rate than previous wars and was caused predominantly by explosive (73%) and gunshot (27%) injuries [5]. The increased vascular trauma rate may be attributable to improvements in body armor, and increased survivability due to the use of tourniquets and shorter casualty evacuation times [5]. As a follow up to the acute care studies, the DoD team initiated a survey study using the SF-36®, SMFA and a questionnaire to determine the functional outcomes of Service members with extremity vascular injury repairs [16]. Long-term outcomes assessment for this study was limited by the inability of the DoD team to access VA databases.

Similar to military trauma, multiple reports document the acute care of patients with civilian vascular extremity injuries, but limited data on small sample sizes is available for long-term outcomes [17]. Thirteen of 22 patients were available with a mean follow-up of 59 months demonstrating graft patency by duplex ultrasound [17]. Additional studies [18–20] on small numbers of patients with long term follow up used ankle-brachial indices or clinical evaluation, which are often inaccurate methods to assess graft patency [21].

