
Statin use has been associated with increased cardiovascular graft patency, see [28] for recent review. While statins were associated with improved 1 year survival in patients receiving lower extremity grafts for atherosclerotic disease, graft patency was not affected by statin use [29]. Statin use and graft patency remains an open critical question; especially given adverse effects (e.g. myopathy) associated with statin use [30].

*Duplex ultrasound graft surveillance* is the standard of care for monitoring bypass grafts and vascular interventions including vein grafts, angioplasties and/or stents [21, 31–34]. This technique allows the physician to visualize the structure of the blood vessels, how blood is flowing through the vessels and measures the speed of the flow of blood. Duplex ultrasound can also be useful to estimate the diameter of a blood vessel/graft as well as determine if a stenosis/occlusion has occurred. This application has been extensively studied in patients with atherosclerosis as the etiology for requiring intervention [21, 31–34]. However, support for use of duplex ultrasound after vascular interventions performed following traumatic injury is limited [17]. *No information is available regarding the extent to which this standard of care is met either in the VA or DoD for vascular repairs performed in trauma patients.*

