**Table 3 Tab3:** **Indicators of persistent morbidity**

Indicators of persistent morbidity	Data used to identify	Data source
Use of unscheduled or emergency care for vascular issues	DSS Clinic Identifier and ICD-9 Codes	Outpatient (OPC) files; VA-CMS
Use of scheduled care for polytrauma vascular issues	DSS Clinic Identifier and ICD-9 Codes	OPC files; VA-CMS
Long-term use/escalating dose of opioid medications	VA Product, Dose, Day Supply	Pharmacy Benefits Management (PBM) Data; Medicare Part D VA-CMS
	NDC Code	
Trajectory of chronic pain (latent class analysis of pain scores from TRACC)	Pain Score	CDW vitals
Conditions indicative of persistent morbidity (e.g., Venous stasis disease/venous ulcers, lymphedema)	ICD-9 Codes including but not limited to 729.81, 782.3, 729.5, 415.19, 451.11, 451.19 451.83, 451.82, V72.83	PTF, OPC files, VA-CMS
Prescriptions for compression stockings and wound care supplies (e.g., wound vac) indicative of swelling, venous stasis disease	VA Class	PBM Data, VA-CMS Durable Medical Equipment
	XA	
Use of prosthetic/orthotic devices (canes, walkers, special shoes, etc).	Health Care Financing Administration Coding System (HCPCS) Prosthetic and Sensory Aids Service (PSAS) Code;	National Prosthetics database
		CMS Durable Medical Equipment
Additional procedures (open or endovascular) on the injured extremity	CPT-4; ICD-9A procedure codes	OPC/PTF VA-CMS
Chronic antibody use (osteo or other potential infectious issues with the limb)	VA Product	PBM Data; Medicare Part D VA-CMS
Duplex ultrasound, MRA/CTA or angiogram to evaluate the repair	CPT-4 procedure codes including but not limited to 93970, 93971, 93975, 93976, 93978, 93979, 93922, 93923, 93925, 93926, 93930, 93931, 93924	OPC/PTF; VA-CMS
Mean pain scores over 4	Pain Score Mean per year	Corporate data warehouse Vital Signs
Proportion of VA care	Visits VA/ Total Visits	OPC/PTF; VA CMS outpatient/inpatient
Mortality	Date of Death	VA Vital Status file

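### Duplex ultrasound is an exposure in the patency model and also a main means of observing patency, so its coefficient cannot support duplex as a best practice

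*Protocol article*

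**What the plan says.** In the Analytic plan (second aim), the outcome is described first as "the percent patency each year for individuals without amputation". The model then "models the vascular repair patency as a linear function of the indicator of receiving antiplatelet agents, statins, duplex ultrasound", plus covariates and a facility random effect. A binary version follows: "We will also create different cut points (e.g. 75%, 50% patent), and use a binary outcome model". The protection offered is weighting: "the inverse of the propensity score for receiving antiplatelet agents/statins/yearly duplex ultrasound is adjusted for as weights". The stated purpose is that this "will minimize the estimation biases due to confounding by indication". The same section says that positive associations would lend support to these care processes as best practices.

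The Background describes how patency becomes known. On duplex it says: "Duplex ultrasound can also be useful to estimate the diameter of a blood vessel/graft as well as determine if a stenosis/occlusion has occurred". Of earlier follow-up studies it says that they "used ankle-brachial indices or clinical evaluation, which are often inaccurate methods to assess graft patency".

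Study procedures lists three components: existing DoD and VA data, VA chart abstraction, and a patient interview and survey. None includes an imaging visit. Table 3 lists "Duplex ultrasound, MRA/CTA or angiogram to evaluate the repair" among the indicators of persistent morbidity.

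**The concern.** In the duplex term, whether and how well the outcome is measured depends on the exposure. A Veteran with yearly duplex has a yearly look at the repair. For a Veteran without it there are three possibilities:

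- no patency value for that year;
- a value from methods that the article itself calls inaccurate;
- a value from an occasional duplex, MRA/CTA or angiogram, probably done because something was wrong.

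Comparing the two groups then partly compares ways of finding out. Table 3 adds to this, because the same kind of scan counts as preventive care in the second aim and as a sign of persistent morbidity elsewhere.

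At stake is the best-practice conclusion. A measurement artefact could appear to endorse surveillance or to discredit it.

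**Working it through.** **The plan's own figure.** The Analytic plan states power of at least 0.84. The inputs are N of about 700 (Study sample), at most 44.7% receiving the services, mean patency of 50%-60%, and an increase of at least 12%, read here as percentage points. Alpha and the test are not given; I assume two-sided 0.05 and a comparison of two proportions. The groups are 700 × 0.447 = 313 and 387.

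- 50% vs 62%: power 0.890
- 60% vs 72%: power 0.916

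Both satisfy the stated bound. The difficulty is not in this calculation, which takes patency as equally well known in both groups.

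**Does weighting reach the problem?** The weights model who receives the service. They can balance measured covariates between receivers and non-receivers. They cannot supply patency that was never observed in unscanned Veterans, or correct patency observed with a different error.

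**Illustration of size.** Take true patency of 55% in both groups (the midpoint of 50%-60%) and no effect of duplex. Assume that patency is fully and correctly known under yearly duplex. In the others, let s_p and s_o be the probabilities of imaging for patent and occluded repairs. The documents give no such rates; those below are assumptions.

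*(a) Only imaged repairs are analysed.* Observed patency without yearly duplex = 0.55 s_p / (0.55 s_p + 0.45 s_o).

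| s_o | s_p | Observed patency | Apparent duplex effect |
|---|---|---|---|
| 0.60 | 0.15 | 0.0825/0.3525 = 23% | +32 points |
| 0.50 | 0.25 | 0.1375/0.3625 = 38% | +17 points |
| 0.40 | 0.30 | 0.1650/0.3450 = 48% | +7 points |

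*(b) Unimaged repairs are counted as patent.* Observed patency = 0.55 + 0.45 (1 − s_o).

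| s_o | Observed patency | Apparent duplex effect |
|---|---|---|
| 0.60 | 73% | −18 points |
| 0.50 | 77.5% | −22.5 points |
| 0.40 | 82% | −27 points |

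**A true benefit can vanish.** Suppose true patency is 61.7% with duplex and 49.7% without, a real 12-point gain. Suppose also that unscanned repairs count as patent unless the occlusion shows clinically, and that 75% of occlusions do. Observed patency without duplex is 1 − 0.503 × 0.75 = 62.3%. The apparent effect is 61.7 − 62.3 = −0.6 points.

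**No coding rule rescues the term.** If 44.7% is taken as an upper limit for yearly duplex, at most about 313 of 700 have yearly imaging. Restricting to imaged Veterans leaves an unexposed group made up only of those who happened to be scanned. Including unimaged Veterans means imputing or misclassifying their outcome.

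**The case against.** The strongest reply is that this is a condensed article. It does not define how patency is ascertained, and the chart-abstraction template is not shown. That is fair as to the definition, and the missing definition is not the point here. A definition alone would not free the duplex term from dependence on scanning; that needs ascertainment independent of the exposure, or a different outcome.

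The separation is also incomplete. The propensity exposure is yearly duplex, so Veterans without it may have an occasional duplex, MRA/CTA or angiogram, and Table 1 lists DoD follow-up imaging. This stands: one should not infer that Veterans without yearly duplex have no patency value at all. Such scans are probably selected by symptoms, though, so the bias remains.

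Three other stronger readings are not supported:

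- *The plan codes unscanned repairs as patent.* It states no such rule; case (b) is only an illustration.
- *The spurious association can be of any size.* With 55% patency and the formulas above it is bounded: at most +55 points, when no patent repair is imaged, and at worst −45, when no occluded one is.
- *The antiplatelet and statin terms are biased in the same way.* They are affected only so far as users are imaged more or less often than non-users, and the documents give no such figures.

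Finally, the study is observational, calls its results a first step, and words the best-practice sentence conditionally. The Aims section also foresees relating preventive care to persistent morbidity. This lowers the stakes and makes the repair easier, but the duplex-patency coefficient remains uninterpretable.

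**Conclusion.** The point holds for the duplex term. Duplex is both an exposure and a main means of observing the outcome, no imaging independent of exposure is described, and the named safeguard is directed at a different bias. The coefficient cannot serve as evidence for or against duplex surveillance.

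This conclusion is structural and does not depend on the illustrative figures. The range of about −27 to +32 points, against the planned 12, rests wholly on the assumed imaging rates, 55% true patency, no true effect, and complete and correct ascertainment under yearly duplex. Neither the sign nor the size of the actual bias can be derived from the documents.

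**What to change.** 1. Remove duplex ultrasound as a predictor in the patency model.
2. Relate duplex surveillance, as a time-updated exposure, to outcomes the study already records without a scan: late amputation and limb salvage survival time (Analytic plan, first aim) and unscheduled vascular care (Table 3). Confounding by indication remains here and still needs the planned weighting.
3. For antiplatelet agents and statins, report the imaged fraction per year by exposure group. Analyse patency in imaged patient-years with inverse-probability-of-imaging weights. State that this assumes imaging is independent of patency given the covariates. The weights do not cure imaging that depends on patency itself, as in case (a), so add a sensitivity analysis for departures from the assumption.

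The cost is revised analysis wording, one further weighting model and a sensitivity analysis. The analysable N for patency becomes smaller, and amputation events may be few for the duplex analysis. The stated power of at least 0.84 would no longer apply to duplex, and precision for the new outcomes would have to be worked out separately.
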